### Whole grain intake outcomes

The American Association of Cereal Chemists International (AACCI) definition of whole grain is applied in the present trial. According to the AACCI, whole grain includes cereal grains that consist of ground, cracker or intact grains, which incorporate all of the components of natural grain, including the endosperm, bran and germ (American Association of Cereal Chemists (AACC) International 2000). The components are present in the same relative proportions in whole grain cereals as they exist in the intact grain. For the purpose of the GReat-Child Trial, whole-grain foods are defined as foods made with at least one whole grain ingredient. All foods containing whole grain ingredients are included, regardless of the amount of whole grain they contained. The children who consumed a whole-grain food on at least one of the recall days are defined as whole grain consumers (Katcher et al. 2008). The amount of whole grain per 100 g in each of the whole-grain foods is estimated from the food label, or directly obtained from the food manufacturer. The whole grain values obtained per 100 g are then multiplied by the actual weight of the food consumed and divided by 100.

### Knowledge, attitudes and practices towards whole grain outcomes

The knowledge, attitudes and practices (KAP) towards whole grain among the children are assessed using a validated, guided, self-administered questionnaire. The details of the KAP towards the whole grain questionnaire, as well as the development and validation procedure have been previously published (Koo et al. 2016a). However, for the sake of completeness, a brief description is provided here. The questionnaire is constructed in the Malay language, and consists of four main sections: (1) demographic factors, (2) knowledge domain, (3) attitude domain and (4) practice domain. The demographic factors are intended to discover the demographic and whole grain consumption pattern. Whereas, the knowledge domain reflects the knowledge on general nutrition and whole grain information, including the food pyramid, source of carbohydrates, definition of whole grains, source of whole grains, nutritional content of whole grains and the benefits of whole grain consumption. The attitude domain is defined as the school children’s opinions and beliefs towards whole grain consumption, awareness and socio-cultural perspectives. Finally, the practice domain corresponds to the school children’s practice towards whole grain consumption, such as the frequency of the intake of whole grain ready-to-eat cereals, whole-grain bread, corn, whole-grain biscuits, oats, barley and brown rice.

### Physical activity measurement outcome

In the GReat-Child Trial, physical activity is measured using a pedometer, Digi-walker CW-701 (Yamax, Fukuyama, Japan), which measures step counts during the children’s waking hours over seven consecutive days for the intervention and control groups. The children are instructed to wear the pedometer on a waist belt, at all times, except while sleeping, swimming and showering. The pedometer has a memory recall to allow the investigator to recover the step counts, and a weighted average daily step count is calculated from the weekdays and weekend days. A minimum number of valid days (at least 3 weekdays and 1 weekend day) are used for the calculation of the average pedometer step counts (Laurson et al. 2008). The pedometer step counts are considered valid if the weighted average step counts are more than 1000 steps per day (Duncan et al. 2006), and the children wear the pedometer for at least 10 h per day (Laurson et al. 2008).

### In-depth interview outcomes

At the conclusion of the GReat-Child trial (9th month), mothers from the intervention group will be invited to participate in an in-depth interview after the second post-intervention, to identify the obstacles they had encountered in increasing whole grain consumption, as well as the changes in the attitudes and practices of their children. This session is important for investigating the sustainability of the present trial, and providing greater insights into the acceptance of whole grain among Malaysian children. Our unpublished preliminary data showed that majority of the children’s food (92.1 %) were prepared by their mother, which is line with the study of Campbell et al. (2007) that also showed that mothers played an important role in children’s dietary habits. Hence, the in-depth interviews involve only mother instead of both parents. The data is collected using semi-structured telephone interviews, and the entire interview conversations are audio-taped and transcribed verbatim. Field notes are taken during and immediately following each phone interview, with regards to the thoughts and ideas of each interviewee.

### Statistical analyses

Statistical analysis is conducted using the SPSS version 22.0 (IBM SPSS Statistics 2014). Data are entered, cleaned and checked before data analyses. Each variable is examined for normality distribution using the Kolmogorov–Smirnov test. Categorical data will be presented as number and percentage. Continuous data will be presented as mean and standard deviation or median and range. Association between categorical variables items and the two groups (intervention and control groups) are determined using Chi square test. The differences between intervention and control group across anthropometric measurements, pedometer step counts, whole grain and dietary intakes, as well as scores of KAP towards whole grain are determined using independent *T* test and Mann–Whitney U test. Analysis of covariance for repeated measures (ANCOVA) is performed to determine the intervention effects, such as the differences in anthropometric measurements, pedometer step counts, whole grain and dietary intakes, as well as scores of KAP towards whole grain between the intervention and control groups. Three models were examined, including (1) within group difference based on time; (2) between group differences regardless of time and (3) between group differences with regard to time. Baseline variables are considered as confounders in each models in order to prevent bias. Model assumptions including normality of the residuals, homogeneity of variance, compound symmetry and homogeneity of regression will be verified. P-value of less than 0.05 for a two-sided test is considered statistically significant.

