**Fig. 1 Fig1:**
[figure not shown]
Flow diagram of the GReat-Child trial design

The standard deviation (SD) of the BMI-for-age z-score obtained from a previous study (Madsen et al. 2009) is taken into consideration for the sample size calculation of this present trial. With the SD of the BMI z-score equal to 0.10, giving a detectable difference of 0.08, a sample size of around 25 children per group at 12 weeks would give 80 % power at the 0.05 significance level. The sample size was estimated using the following equation (Naing 2009):$$ {\rm n} =[2 \upsigma^2/\Updelta^2]  ({\rm Z}_{\upalpha}+{\rm Z}_{\upbeta})$$where n = estimated sample size, σ = standard deviation for BMI-score from previous study = 0.10, ∆ = detectable difference = 0.08, Z_α_ = significance level for two-sided test = 1.96, Z_β_ = 80 % power of study = 0.84.

The sample size required for this study is 25 per group. While taking into account a non-response rate of 50 %, the required sample size for each group is increased to 38; therefore, the total number of children needed is 76. Any children who wish to dropout are allowed to do so, with the reasons being noted and analysed.

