### Intervention outcome measurements

The children are assessed on three occasions, at the baseline, at the thirteenth week and at the ninth month. All the assessments are done by one investigator throughout the study to avoid the problem of inter-interviewer variations.

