### Anthropometric measurement outcomes

The primary outcome measured is the BMI-for-age z-score, which is compared between the intervention and control groups. The body weight and height of each child are measured twice, according to standard procedures, using a calibrated Tanita digital scale Model SC-330 (Tanita Co., Tokyo, Japan) and SECA Bodymeter 217 (SECA GmbH & Co., Hamburg, Germany), respectively. The measurements are recorded to the nearest 0.1 kg and 0.1 cm, respectively. The body mass index (BMI) of each child is calculated by dividing the measured weight (kg) by the square of the height (m). The World Health Organization (WHO) BMI-for-age growth reference for children aged 5–19 years old (30) served as the standard reference for determining the nutritional status of the children. The z-scores for BMI-for-age (BAZ) are determined using the software WHO AnthroPlus version 1.0.3, and children are classified into overweight (BAZ +1SD to +2SD) and obese (BAZ > +2SD) categories. The percentage of body fat is measured twice by bioelectrical impedance using the TANITA digital scale Model 300GS (Tanita Co., Tokyo, Japan) and nearest to 0.1 %. The children stood bare footed on the scale, after the electrode of the scale is cleaned to remove any debris. Any objects that could interfere with the readings are removed from their pockets before the measurements are taken.

Waist circumferences (WC) of the children are measured twice, according to the standardised protocol by the National Health and Nutrition Examination Survey (NHANES), which assessed the WC just above the right iliac crest at the mid-axillary line (Centers for Disease Control and Prevention National Health and Nutrition Examination Survey 2000). The WC is measured to the nearest 0.1 cm by using a Lufkin tape model W606PM (Apex Tool Group, Maryland, USA). Finally, the reported values of the body weight, height, percentage of body fat and WC are the average values from the two readings taken.

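### Repeated-measures ANCOVA, read as the classical procedure, drops children who miss month 9 from the adjusted 12-week comparison; a mixed model in the same software keeps them

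*Protocol article*

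**What the plan says.** Under Intervention outcome measurements, children are assessed "at the baseline, at the thirteenth week and at the ninth month". Under Anthropometric measurement outcomes: "The primary outcome measured is the BMI-for-age z-score, which is compared between the intervention and control groups". The sample-size paragraph sets the time point: "a sample size of around 25 children per group at 12 weeks would give 80 % power at the 0.05 significance level". It raises 25 per group to 38 for a 50 % rate that it calls non-response, without dividing this between refusal, loss before week 13 and loss by month 9. On dropout it adds: "Any children who wish to dropout are allowed to do so, with the reasons being noted and analysed".

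Statistical analyses gives the intervention effects to one method: "Analysis of covariance for repeated measures (ANCOVA) is performed to determine the intervention effects". Baseline variables enter each model as confounders, and the models cover change over time, group, and group with regard to time. The section continues: "Model assumptions including normality of the residuals, homogeneity of variance, compound symmetry and homogeneity of regression will be verified". It also plans independent t and Mann–Whitney tests between groups. The software is SPSS 22.0. The article does not name the procedure or say how a child with only one follow-up is used.

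**The concern.** Classical repeated-measures ANCOVA (SPSS GLM) needs a complete row of repeated measures for each child. A child with a valid week-13 z-score but no month-9 visit leaves the whole model, including its week-13 contrast. The comparison the trial was sized for would then depend on attendance about six months later.

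Two things are at stake. The first is precision, because week-13 values already measured are not used. The second is bias. One school has daily supervised food, classes and parent counselling, while the other has no intervention activities until the trial ends, so retention could differ between schools. If children whose week-13 result was poor are less likely to return at month 9 in one school, the children seen at both visits are a selected group.

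**Working it through.** **Inputs.** From the sample-size paragraph: σ = 0.10, Δ = 0.08, 80 % power, 25 per group raised to 38, and a 50 % rate. From Statistical analyses: two-sided α = 0.05. Assumed, because the plan does not give it: how the loss divides between the periods before and after week 13. No child is assumed to miss week 13 and then return.

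**The plan's own figure.** n = 2σ²/Δ² × (1.96 + 0.84)² = 2 × 0.01/0.0064 × 7.84 = 24.5, so 25. The printed formula lacks the square and would give 8.75; the stated 25 matches the squared form. The 38 is 25 × 1.5 = 37.5, rounded up. A true 50 % loss from 38 leaves 19. Ending with 25 of 38 corresponds to a loss of 13/38 = 34.2 %.

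**Power formula.** Power ≈ Φ(Δ / (σ√(2/n)) − 1.96). At n = 25: 0.08/(0.10 × √0.08) = 2.83, so Φ(0.87) = 80.7 %, which agrees with the plan.

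**Scenario A: 50 % of 38 lost by month 9.** 19 per group have both follow-ups whatever the split. Power at n = 19 is Φ(2.47 − 1.96) = 69.4 %.

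| Share of loss before week 13 (assumed) | Seen at week 13, per group | Week-13 values discarded, per group | Power, all week-13 values | Power, both follow-ups only |
|---|---|---|---|---|
| 0 % | 38.0 | 19.0 | 93.7 % | 69.4 % |
| 25 % | 33.2 | 14.2 | 90.4 % | 69.4 % |
| 50 % | 28.5 | 9.5 | 85.5 % | 69.4 % |
| 75 % | 23.8 | 4.8 | 78.7 % | 69.4 % |
| 100 % | 19.0 | 0 | 69.4 % | 69.4 % |

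For the middle row, the t distribution gives 84.3 % against 67.0 %. The standard error is √(28.5/19) = 1.22 times as large.

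**Scenario B: loss of 34.2 %, leaving 25.** The number discarded runs from 0 to 13 per group. With an even split, 31.5 are seen at week 13, 6.5 are discarded, and power is 88.8 % against 80.7 %.

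**Simulation of the middle row** (4,000 runs, 38 per group, 25 % lost before week 13 and 50 % overall, t tests on the week-13 value). The test on all week-13 values stands in for an unstructured mixed model, because the loss is monotone. With dropout unrelated to outcome and a between-visit correlation of 0.5, power is about 84 % with all values and 66 % with children seen at both visits.

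**Bias illustration.** Suppose that, in the intervention school only, the log-odds of dropping out after week 13 rise by 0.7 per SD of the week-13 value. This mechanism is assumed. The both-visits estimate averages about −0.095 against a true −0.08; all week-13 values give −0.080. With no true effect (correlation 0.8), the type I error is 9.3 % for children seen at both visits and 4.8 % for all week-13 values.

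**Compound symmetry.** With baseline as a covariate, the repeated outcomes are week 13 and month 9. Two occasions give one within-child contrast, so sphericity holds automatically. The assumption has force only if baseline is a third level of time.

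**The case against.** Four stronger readings are tempting, and the article does not support them.

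- **That the plan prescribes complete-case analysis.** It does not. No SPSS procedure or missing-data rule is stated, and compound symmetry is also a covariance option in SPSS MIXED. Deletion is inferred from the method's name and from the list of checks, which includes homogeneity of regression. That is the natural reading, but still an inference. Detailed missing-data rules may sit in a document not shown. The point here is the choice of method, which the article does fix.
- **That the plan expects to lose half its children by month 9.** The 50 % is called non-response and is not split by visit. If it is all refusal or loss before week 13, no observed week-13 value is discarded and a mixed model gains nothing for that contrast.
- **That a failure of compound symmetry makes the group-by-time P-value wrong.** With baseline as covariate and two follow-ups this does not follow. Unequal spacing of visits does not by itself violate the assumption either.
- **That week-13 data would go wholly unused.** The planned t and Mann–Whitney tests can use every child seen at week 13. They do not adjust for baseline, however, which matters when schools are assigned without randomisation, and the article gives the intervention effects to the ANCOVA.

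Two further objections stand as limits. A completers' ANCOVA remains valid if dropout depends only on group and the baseline covariates, and a mixed model is also biased if dropout depends on unobserved values. The power figures are at child level and ignore the one-school-per-arm design.

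**Conclusion.** The point holds conditionally. If the ANCOVA is run in its classical form and any children are lost between week 13 and month 9, their week-13 values leave the adjusted comparison on which the trial was sized. With 50 % of 38 per group lost by month 9, the cost is 0 to 19 values per group. At an even split it is 9 to 10 values, with power falling from about 84–85 % to 66–69 %. These figures rest on the plan's SD and difference, independent children, and an assumed timing of loss. The bias is a possibility under an assumed dropout mechanism, not a prediction. Compound symmetry is a side issue unless baseline is entered as a third time level. The change is worth making because it is cheap and removes the dependence of the week-13 result on month-9 attendance.

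**What to change.** Replace the repeated-measures ANCOVA for the primary outcome with a linear mixed model for repeated measures (SPSS MIXED, REML):

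- outcomes: BMI-for-age z-score at week 13 and month 9;
- fixed effects: group, visit, group by visit, baseline z-score and baseline z-score by visit;
- unstructured covariance between the two follow-ups;
- all children with at least one follow-up;
- the week-13 group contrast named as primary.

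Report dropout and its reasons by school and by visit, using the reasons already to be collected. The unstructured covariance also settles the compound-symmetry question.

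The cost is a change of wording and slightly more analysis work, with no new data or software. The model relies on data being missing at random given baseline, group and the observed follow-up. It does not repair the design with one school per arm, nor the inflation that yields 38 where 25/(1 − 0.5) would give 50.

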## Discussion

The childhood obesity epidemic is one of the biggest current challenges for health policy; therefore, effective interventions to manage childhood obesity are needed. This, will in turn improve the health status of children and reduce the economic burden of obesity. A significant reduction in BAZ has been reported in a cross sectional study, which examined the relationship between the intake of whole grain and BAZ (Choumenkovitch et al. 2012); however, none of the experimental studies examined the effectiveness of whole grain consumption intervention in managing childhood obesity. To the best of our knowledge, this is the first multi-component, family-based intervention study focussing on whole-grain combined with healthy balanced diet to manage childhood obesity.

The essential elements of interventions are likely to include dietary modifications and nutrition education (Kirk et al. 2005). For example, one previous study demonstrated that when nutrition education was used as an intervention strategy, there was an improvement in nutrition knowledge, attitudes and eating behaviours (Prelip et al. 2011). Therefore, six 30-min nutrition education classes are included in the GReat-Child Trial, which aimed to improve the level of the KAP towards whole grains among the children. The duration of the nutrition education classes is only 30 min per session, as a previous study has shown that students typically have short attention span of only 10–15 min (Bunce et al. 2010).

Several studies from different countries and continents, including Malaysia (Koo et al. 2016b), Bahrain (Nadia and Parveen 2011) and Europe (Kleiman et al. 2012), have demonstrated that children lack dietary fibre and several micronutrients in their diets, despite having adequate calorie and macronutrient intakes. These studies also revealed that fibre insufficiency was apparently due to low consumption of vegetables, fresh fruits and other sources of fibre, such as whole grain, legumes and high fibre cereals, as observed in diet recalls. The micronutrient deficiencies may increase the risk of childhood obesity, due to fat deposition and chronic inflammation (Garcia et al. 2009); however, dietary cereals enriched with whole grains appeared to be more useful in the maintenance of adequate micronutrients and increasing the levels of fibre (Ortega et al. 2009). Therefore, the GReat-Child Trial is conducted with an emphasis on whole grain as a strategy to manage childhood obesity.

Low consumer awareness, confusion about the identification of whole grains, limited availability and disinclination to the taste of whole grain foods, texture and colour are the most habitually cited obstacles for the consumption of whole-grain foods (Burgess-Champouxt et al. 2006). According to Freeland-Graves and Nitzke (2007), the outcomes of an intervention are more likely to be positive if an organisation includes the activities that reflect the targetted school-aged children’s culture, lifestyle and preferences, as well as distribution of food samples in the intervention programs. Thus, to provide the opportunity for children to experience and embrace a healthy new repertoire of whole grain alternatives in their diets, the GReat-Child Trial offered one serving of whole-grain foods to the children on a daily basis, by replacing refined-grain foods with various types of wholegrain counterparts. In addition, the present trial involved greater contact time with the children and included the parents, unlike a quasi-experimental trial from the US which involved school cafeteria workers, and aimed to increase the whole grain consumption among children (Burgess-Champouxt et al. 2007). Modifications are made in order to place the parents as the main agents of change, because this approach was successful in a previous Malaysian randomized controlled trial that aimed to manage childhood obesity (Wafa et al. 2011).

Social marketing and recipe modification strategies had been applied in previous interventions to successfully modify fat intake (Ellison et al. 1989), vegetable and fruit intakes (Reynolds et al. 2000), as well as intake of low-fat milk (Wechsler et al. 1998). The outcomes of these interventions showed improvements in consumption of low-fat milk, low-fat diet, vegetables and fruits due to the food preparation practices, where these interventions provided them with convenient, palatable and easy to prepare options. In the present study, the selected whole-grain foods included whole-grain bread, whole-grain ready-to-eat cereals and whole-grain biscuits, because these were convenient and nutrient-dense, and did not require complicated preparation. Encouragingly, a recent study of 10–11 years old Malaysia schoolchildren in Kuala Lumpur reported that bread, biscuits and ready-to-eat cereals were the most commonly eaten foods at breakfast (Koo et al. 2015b). In addition, ready-to-eat cereal consumption showed an inverse association with BMI and waist circumferences (Koo et al. 2014).

The main strength of the GReat-Child Trial is that it represents a novel approach to examine the effectiveness of intervention with whole-grain and healthy balanced diet in managing childhood obesity. We anticipate that this study will not only reveal if an intervention focussing on consumption of whole grain in combination with healthy balanced diet will be effective, but that it will also provide greater insights into the acceptance of whole grain among Malaysian children. Longer duration of intervention may produce better outcomes in managing childhood obesity, but such interventions are much less likely to be practical (Wafa et al. 2011). The efficacy of the GReat-Child Trial described in this paper is not conclusive, as the study is still on-going, and further outcomes will be published in the near future.

